### 3.4. Ethics and Registration

This study will adhere to the ethical standards set forth by the Declaration of Helsinki (Edinburgh, 2000), ISO standard 14155 [39], and all other applicable device and Spanish regulations. Approval from the appropriate institutional review board (IRB) will be obtained with informed consent collected from all participants. Researchers and therapists will closely monitor participants to prevent clinical deterioration, and post-treatment assessment will capture any adverse or unwanted events.

### 3.5. Statistical Analysis

The primary analysis will employ linear mixed-effects models (LMMs) to compare changes in MOXO CPT total score over time between groups. Fixed effects will include treatment group, time, and their interaction, with random intercepts for participants to account for within-subject variability. Demographic factors such as age, gender, and ADHD presentation will be included as covariates.

Secondary analyses will follow a similar approach, using generalized linear mixed models (GLMMs) for outcomes like ASRS scores and LMMs for continuous measures of cognitive performance. Clinically significant improvements in ADHD symptoms, defined as a ≥12-point reduction in ASRS scores, will be analyzed using logistic regression.

Exploratory analyses will assess the durability of treatment effects over a 1-month follow-up period, using additional time points in the mixed-effects models. Correlations between cognitive and functional measures, particularly CPT indices (e.g., omissions and concentration) and ASRS scores, will be explored using Pearson or Spearman correlation coefficients, with the false discovery rate (FDR) method applied to control for multiple comparisons.

To address potential missing data, logistic regression will be used to determine whether missingness is random or systematic. Multiple imputation methods [40] will be employed to account for missing values, and sensitivity analyses will be conducted to compare complete-case results with those from imputed datasets, ensuring robustness. Model selection will be guided by the Bayesian Information Criterion (BIC), and diagnostics will include residual checks to validate model assumptions.

All analyses will be conducted using R (version 4.3.1, 2025) or JASP (version 0.19.1, 2024). For linear mixed-effects models, we will use the lm4 package in R; for generalized models, the glmmTMB package will be applied. Missing data will be handled using the mice package (Mice 3.16.0) for multiple imputation. Residual diagnostics and model assumptions will be evaluated using performance and DHARMa. Correlation analysis will be conducted using base R or psych (R 4.5.0; Psych package 2.5.), with *p*-values adjusted using the Benjamini–Hochberg method to control the false discovery rate. This comprehensive approach will ensure robust evaluation of the efficacy and potential long-term benefits of Sincrolab Adults, while exploring associations between cognitive and functional outcomes in adults with ADHD, thereby assessing the value of Sincrolab as a non-pharmacological treatment option.

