## 3. Materials and Methods

### 3.1. Design and Participants

This study is a parallel, randomized controlled trial (RCT) with a treatment-as-usual control group, employing a single-blind design to minimize bias. (Outcome assessors will be blinded to group allocation).

This study will include 104 adults aged 18 and older to evaluate Sincrolab Adults (v.4.0.24) (60% male/40% female, reflecting ADHD prevalence in Spain). The study will consist of adults with ADHD, with any presentation, who are stable on or off medication doses (for at least 2 weeks prior to baseline) and present persistent/stable symptoms (ADHD-RS ≥ 28). Participants will be divided into two equally sized groups (n = 52) that will either receive Sincrolab Adults or be placed in the control group.

The Sincrolab’s medical device consists of 14 tasks/games distributed across training sessions. Each training session includes a predetermined number of tasks, ensuring that different tasks are trained on each day. Each of the 14 tasks/games has a series of parameters that define them and allow for the identification of the cognitive processes involved (e.g., number of stimuli, number of distractors, stimulus speed, inter-stimulus interval, etc.). The intervention supports (a) the integration of various cognitive processes within each rehabilitation task/game; and (b) the adaptation of difficulty levels across the 14 tasks/games that make up the tool, based on each user’s performance in previous training sessions. The algorithms within the patented AiSA© artificial intelligence system adjust the difficulty level of cognitive stimulation tasks. Once AiSA has data on the participant’s performance during the initial cognitive training sessions, it uses this information to personalize the difficulty level of the tasks for each session and participant. In this way, cognitive training is completely personalized to each user.

The sample size per group in a two-sample design was calculated based on previous results [32] and using a moderate effect size (d = 0.62), as this provides a measure of the treatment effect. The required sample size will also assume a 20% dropout rate, resulting in 104 total participants, 52 per group.

The formula for the sample size per group in a two-sample design from Cohen (1988) [38] is used:n = 2⋅(z_α/2_ + zβ)^2^/d^2^

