where:z_α/2_: Critical value for the significance level (α = 0.05) = 1.96.zβ: Critical value for power (1 − β = 0.801) = 0.84.d: Effect size (d = 0.62).n: Sample size per group.

The study protocol (Figure 1) will span 12 weeks plus an additional month of follow-up, with three assessments (baseline, post-intervention, and follow-up). Participants in the intervention group will use a digital cognitive training program designed to target multiple cognitive functions associated with ADHD dysfunctions. The program will include adaptive training games that can be played on a computer or mobile device. Participants will play the training games 3 to 5 times per week, for 15 min per session, over a 12-week period. Participants in the control group will not receive the intervention during the 12-week trial but will be offered access to the program after the study concludes.

The study flow diagram is as follows:

Inclusion criteria.

Participants must meet all of the following:○Adults aged 18 and older○Clinical diagnosis of ADHD according to DSM-5 criteria, confirmed using the DIVA 5.0 Interview for Attention-Deficit/Hyperactivity Disorders Studies (Adult version)○Stable use or non-use of ADHD medications for at least 2 weeks prior to enrollment and throughout the 12-week study period○Baseline ADHD-RS score ≥ 28○Ability to understand and follow written and verbal instructions in Spanish, as assessed by the Principal Investigator or study coordinator○Completion of the informed consent form○Access to a compatible digital device○Willingness and ability to comply with all study procedures and testing requirements

Exclusion criteria.

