### 3.6. Expected Outcomes

Results will be reported in accordance with the CONSORT 2010 guidelines.

The primary outcome will be reported as the change from baseline to post-intervention in MOXO CPT total score, presented as estimated marginal means with standard errors for each group, along with 95% confidence intervals and effect sizes (Cohen’s d). It is anticipated that participants in the Sincrolab Adults group will show greater improvement compared to the control group.

Secondary outcomes (e.g., ASRS scores) will be reported as mean changes, proportions of participants achieving clinically significant improvement (defined as a reduction of 12 points or more on ASRS), and corresponding odds ratios and confidence intervals. It is expected that the Sincrolab Adults group will exhibit a greater reduction in ASRS score and a higher proportion of participants achieving a clinically significant improvement compared to the control group.

Exploratory outcomes (AAQoL scores, additional MOXO indices) will be presented as mean (±standard deviation) pre–post changes for each group, along with group × time interaction *p*-values and effect sizes for each exploratory measure. Participants in Sincrolab Adults are expected to show greater pre–post gains in quality of life and MOXO sub-indices compared with controls. We anticipate positive correlations between improvements in CPT indices and improvements in functional outcomes (ASRS) and quality of life (AAQoL). Finally, we expect treatment benefits to be maintained at the 1-month follow-up.

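### Adjusting the primary analysis for baseline MOXO score would gain precision at no cost; the planned mixed model is valid but tests an unadjusted difference in change

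*Protocol article*

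**What the plan says.** Section 3.5 of the protocol article compares the arms on change in MOXO CPT total score with a linear mixed model: "Fixed effects will include treatment group, time, and their interaction, with random intercepts for participants to account for within-subject variability". On covariates it adds: "Demographic factors such as age, gender, and ADHD presentation will be included as covariates". Baseline MOXO score is not named as a covariate, the arms are not given a common mean at baseline, and no covariate-by-time term is stated.

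Section 3.6 confirms the primary quantity: "change from baseline to post-intervention in MOXO CPT total score".

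Section 3.1 sizes the trial with a standard formula for two independent groups: "The sample size per group in a two-sample design was calculated based on previous results", "using a moderate effect size (d = 0.62), as this provides a measure of the treatment effect". The other inputs are "Critical value for the significance level (α = 0.05) = 1.96", "Critical value for power (1 − β = 0.801) = 0.84" and 20% dropout, giving 52 per arm and 104 in total. No SD, no baseline-to-post correlation and no scale for d is given.

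**The concern.** In a randomised trial the two arms have the same expected score at baseline. A model with a free group effect at baseline spends information on estimating a difference known to be zero in expectation, and then subtracts that noisy estimate from the post-intervention difference. The subtraction over-corrects chance imbalance whenever the baseline predicts the post score imperfectly. Using baseline as a covariate, or giving both arms one baseline mean, avoids this and in large samples is never less efficient.

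The covariate sentence may also suggest that the primary contrast is already adjusted. Age, gender and presentation do not vary within a participant, so as main effects they drop out of a within-participant change.

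What is at stake is the precision of the single primary test in a trial of 104 people. The baseline score is already collected, so the gain needs nothing new.

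**Working it through.** **1. The plan's own figure.** Inputs from section 3.1: z = 1.96 and 0.84, d = 0.62, dropout 20%.

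- n = 2(1.96 + 0.84)²/0.62² = 40.79, so 41 evaluable per arm.
- 41/0.8 = 51.25, so 52 enrolled per arm, 104 in total. This matches.
- Power at 41 per arm is 80.2% by the normal formula (stated: 80.1%) and 79.2% by the t distribution.

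**2. What the stated model estimates.** The model was fitted to simulated data with 52 per arm and two visits.

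- *Complete data:* in one data set the group-by-time estimate was 0.6831 (SE 0.2408), identical to the difference in raw change scores. Adding age and sex left the estimate unchanged and the SE the same to about five decimals.
- *About 20% of post scores missing:* adding the covariates changed the SE from 0.2811 to 0.2802, 0.2151 to 0.2124, and 0.1573 to 0.1570 in three data sets, so by 0.3%, 1.2% and 0.2%. The estimates moved slightly too, for example from 0.565 to 0.542.
- *Baseline MOXO as one more main effect:* in complete data this also left the contrast exactly unchanged, because baseline remains an outcome row.

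**3. Variance with and without baseline adjustment.** ρ is not in the article and is varied as an assumption. With a common SD s at both visits:

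- change score: 2s²(1 − ρ)
- baseline-adjusted: s²(1 − ρ²)
- ratio, adjusted to change: (1 + ρ)/2, a reduction of (1 − ρ)/2

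| Assumed ρ | Variance ratio | Reduction | 41 adjusted completers per arm are worth |
|---|---|---|---|
| 0.3 | 0.65 | 35% | 41/0.65 = 63 |
| 0.5 | 0.75 | 25% | 41/0.75 = 55 |
| 0.7 | 0.85 | 15% | 41/0.85 = 48 |

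**4. Unequal SDs.** Let k be the post SD divided by the baseline SD. In baseline-variance units the change variance is k² + 1 − 2ρk and the adjusted variance is k²(1 − ρ²). At ρ = 0.7 and an illustrative k = 1.3:

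- change: 1.69 + 1 − 1.82 = 0.870
- adjusted: 1.69 × 0.51 = 0.862

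The gain is then about 1% instead of 15%. With k below 1 it can exceed the tabulated value.

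**5. Power at 41 evaluable per arm** (normal formula, equal SDs), under both readings of d = 0.62:

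| Assumed ρ | d in raw-score SDs: planned | d in raw-score SDs: adjusted | d in change-score SDs: planned | d in change-score SDs: adjusted |
|---|---|---|---|---|
| 0.3 | 66.0% | 83.7% | 80.2% | 93.6% |
| 0.4 | 72.7% | 86.5% | 80.2% | 91.9% |
| 0.5 | 80.2% | 90.0% | 80.2% | 90.0% |
| 0.7 | 95.2% | 97.6% | 80.2% | 86.1% |

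The planned contrast falls below 80% only in the raw-score reading with ρ under about 0.5.

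**The case against.** The strongest reply is that a group-by-time mixed model is a common and valid analysis of a randomised pre-post trial. It is unbiased, keeps its error rate and matches the change from baseline that section 3.6 reports. This stands: the point is one of efficiency.

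A reader might go further and infer that the trial is underpowered. The article does not support that. Its sample size reproduces, and d is taken from a previous study that is not shown. If d is in change-score SD units, a natural choice for a plan that compares changes, the planned test has its stated power at any ρ. On the raw-score scale it also does so once ρ reaches about 0.5. The 79% obtained with a t distribution at ρ = 0.5 reflects only the normal approximation in the formula.

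It can also be said that the covariate list is open-ended, that interactions with time are not ruled out, that model selection by BIC is planned, and that an article leaves exact parameterisation to a fuller document. This is fair in part. But the article does state the structure of the primary model, the list is of demographic factors, and neither BIC selection nor multiple imputation commits the plan to a different contrast. Lengthening the list does not help either, since even baseline MOXO as a main effect leaves the contrast unchanged.

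Finally, calling the covariates useless would be too strong. Exact cancellation needs complete data; with dropout they have a small effect and can support a missing-at-random assumption.

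**Conclusion.** This is a free improvement to a stated method, not an error of validity. The primary model in section 3.5 estimates the unadjusted difference in change in MOXO total score, and the named covariates as main effects do essentially nothing to sharpen it. Adjusting for baseline would reduce the variance of the treatment effect by 35%, 25% and 15% at ρ of 0.3, 0.5 and 0.7. Those figures rest on two assumptions that the article does not settle: the value of ρ, and equal SDs at the two visits.

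The stated power is neither refuted nor fully pinned down, because the scale of d is not given. Under the equal-SD calculation, baseline adjustment makes the planned 80% a floor on either reading of d, whereas under the stated model it can depend on ρ.

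**What to change.** Before unblinding, replace the primary model in section 3.5 with one of the following:

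- an ANCOVA of post-intervention MOXO total score on arm, baseline MOXO total score, age, gender and ADHD presentation; or
- a longitudinal model with one common baseline mean for both arms (no group effect at baseline) and covariate-by-time terms.

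Adding baseline MOXO as a further main effect to the existing model is not enough.

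In section 3.1, state the SD to which d = 0.62 refers (raw score or change score) and, if raw score, the baseline-to-post correlation assumed. Adding medication status as a covariate is optional and corrects no error.

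The cost is one paragraph of analysis wording and a sentence on sample size. It needs no new data and no more participants.

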### 2.2. Secondary Objectives

The secondary aim is to assess whether treatment with Sincrolab Adults, compared to the control group, leads to significant changes in functional ADHD symptoms as measured using the Adult ADHD self-report Symptom Rating Scale (ASRS) [35]. Additionally, the study aims to evaluate whether these improvements reach clinically significant levels, defined as a minimum change of 12 points between baseline and post-treatment scores [36].

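### The 12-point ASRS responder regression names no baseline ASRS covariate; the test stays valid, but roughly 2 to 11 points of power may be lost, depending on assumptions

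*Protocol article*

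**What the plan says.** Section 2.2 makes clinically significant symptom improvement part of the secondary objective, "defined as a minimum change of 12 points between baseline and post-treatment scores". Section 3.5 gives the method: this outcome, "defined as a ≥12-point reduction in ASRS scores, will be analyzed using logistic regression". Section 3.6 promises the proportion of responders in each group with "corresponding odds ratios and confidence intervals".

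On covariates, the paragraph of section 3.5 on the primary mixed model says: "Demographic factors such as age, gender, and ADHD presentation will be included as covariates". The next paragraph opens with "Secondary analyses will follow a similar approach, using generalized linear mixed models (GLMMs) for outcomes like ASRS scores". No covariate list is given for the responder regression itself, and baseline ASRS is neither named nor excluded. Section 3.5 also says that BIC will guide model selection, without saying which models this covers.

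The article states no ASRS standard deviation, no correlation between baseline and post-treatment scores, no expected responder rates and no power for this outcome.

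**The concern.** A participant responds if baseline minus post-treatment ASRS is at least 12. Someone with a high baseline score has more room to fall and tends to regress to the mean; someone with a low score has less room. Baseline ASRS therefore predicts response, and every participant classified must have it.

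The covariate approach of the primary model does not carry over safely. In a mixed model with group, time and their interaction, the baseline score enters as the first time point. The responder variable reduces two scores to one yes or no per person, and the baseline information is lost unless it is put back as a covariate. Read as written, section 3.5 yields a regression on group, perhaps with demographic factors.

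At stake are the precision and robustness of the odds ratio for the stated criterion of clinically significant symptom benefit. If BIC also governs this model, whether baseline ASRS enters could be decided after the data are seen. Adjusted and crude odds ratios estimate different quantities, so that choice should be made beforehand.

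**Working it through.** **1. The plan's own sample size.** From section 3.1: d = 0.62, "Critical value for the significance level (α = 0.05) = 1.96" and "Critical value for power (1 − β = 0.801) = 0.84". Then n = 2 × (1.96 + 0.84)² / 0.62² = 15.68 / 0.3844 = 40.8, so 41 evaluable per arm. With 20% dropout, 41 / 0.8 = 51.25, so 52 per arm and 104 in total. The stated figures reproduce. They do not concern the ASRS responder outcome.

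**2. How strongly baseline predicts the change.** With equal SDs at both visits and correlation r, the correlation between baseline and the fall from baseline is (1 − r) / √(2(1 − r)) = √((1 − r)/2). This is 0.59 at r = 0.3, 0.50 at r = 0.5 and 0.39 at r = 0.7. The benefit of adjusting should therefore shrink as r rises.

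**3. Power with and without baseline ASRS.** All ASRS inputs are assumptions: SD 8, 10 or 12; r = 0.3, 0.5 or 0.7; mean fall in controls 2 or 5 points; treatment effect 0.62 SD (borrowed from the sample size); bivariate normal scores; 41 or 52 per arm. For each of the 36 combinations, 4,000 trials were simulated. Logistic regression on group alone was compared with group plus baseline ASRS at two-sided 0.05.

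| r | Gain in points, Wald test | Gain in points, likelihood-ratio test | Example (41 per arm, SD 10, control fall 5, Wald power) |
|---|---|---|---|
| 0.3 | 7.1 to 10.7 | 8.3 to 11.5 | 0.457 to 0.536 |
| 0.5 | 3.8 to 8.0 | 5.4 to 7.9 | 0.580 to 0.643 |
| 0.7 | 1.9 to 4.5 | 1.9 to 4.0 | 0.769 to 0.807 |

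A separate simulation with likelihood-ratio tests (41 per arm, 2,000 trials per scenario) gave gains of about 3.5 to 9 points, for example 0.44 to 0.53 at SD 8, r = 0.4, and 0.73 to 0.77 at SD 10, r = 0.7.

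**4. Type I error.** With no effect (41 per arm, SD 10, control fall 5), rejection rates were 0.036 to 0.041 (Wald) and 0.045 to 0.047 (likelihood ratio) for group alone. With baseline added they were 0.040 to 0.047 and 0.054 to 0.056. The crude test is valid. The likelihood-ratio gains are slightly flattered, because the adjusted test rejects a little more often under the null.

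**5. Chance imbalance.** Take no effect, SD 10, 41 per arm and a mean fall of 3. The standard error of the baseline difference is 10 × √(2/41) = 2.2 points. A difference of that size shifts the expected fall by (1 − r) × 2.2 between arms.

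- r = 0.6: responder rates 14.6% and 16.9%, odds ratio 1.20, log odds ratio 0.18. Its standard error is √(1/6.0 + 1/35.0 + 1/6.9 + 1/34.1) = 0.61, so the shift is 0.18 / 0.61 = 0.30 standard errors.
- r = 0.4: 18.9% and 22.3%, odds ratio 1.23, log odds ratio 0.21. Its standard error is √(1/7.7 + 1/33.3 + 1/9.1 + 1/31.9) = 0.55, so the shift is 0.21 / 0.55 = 0.38 standard errors.

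In the simulations with an effect, the crude log odds ratio correlated 0.09 to 0.47 with the chance baseline difference. After adjustment the correlation was −0.03 to 0.05.

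**6. Adding the demographic covariates as well.** Group, baseline ASRS, age, gender and two terms for presentation make six terms. With a control fall of 3 and no effect, only about 12 to 17 responders are expected among 82 participants, or about 2 to 3 per term. In simulations of that model the likelihood-ratio test rejected about 5% to 7.5% of the time under the null, and almost no power was gained over baseline ASRS alone.

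The simulations ignore the ADHD-RS entry threshold and the limits of the ASRS scale.

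**The case against.** The strongest reply is that this rests on silence. The article gives no covariate list for the responder model, introduces the named covariates as examples, and leaves room for a fuller plan that is not shown. That stands in part: baseline ASRS is unnamed, not excluded, and a reader who infers that the plan rules it out goes beyond the text. But the covariates named are described as demographic, which a baseline symptom score is not. The approach to be followed also comes from a model in which baseline needs no covariate. The method as stated is therefore weaker than one available from data already collected.

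A reader might also infer that the crude odds ratio is biased or its type I error inflated. The documents do not support that. Randomisation protects the crude test, the null rejection rates confirm it, and the crude confidence interval already allows for a shift of a third of a standard error.

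Nor can a single figure for the power loss be derived. A loss of 6 to 9 points, for example, fits only low to moderate correlations. Finally, the outcome is secondary, no power is claimed for it, and the main ASRS analysis by repeated-measures model already uses the baseline score. These points limit the importance of the concern but do not remove it.

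**Conclusion.** The point holds as a matter of precision and prespecification, not validity. A change-from-baseline responder outcome is to be analysed by a logistic regression for which no baseline ASRS covariate is named. Under the assumptions in the working, this costs roughly 2 to 11 points of power: about 7 to 11 at a correlation of 0.3 and 2 to 4.5 at 0.7. The direction was the same in every scenario; the size depends on inputs that the article does not give, and the 0.62 SD effect is not tied to ASRS. Sensitivity to chance imbalance is real but modest. This is a worthwhile improvement to a secondary analysis and does not threaten the trial's primary conclusion.

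**What to change.** In section 3.5, state that the 12-point responder outcome will be analysed by logistic regression on treatment group with baseline ASRS total as a continuous covariate, fixed in advance and outside any BIC-guided selection. In section 3.6, report the adjusted odds ratio together with standardised (marginal) responder proportions by group and their difference, with 95% CI.

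Do not require age, gender and presentation in this model, because responders may be few. If they are kept, use a small-sample fit such as Firth-type logistic regression.

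The cost is a sentence or two of wording and no new data. There are two downsides. The adjusted odds ratio is conditional and will differ from the crude one even without imbalance; the standardised proportions deal with that. And the type I error of the likelihood-ratio test can run slightly above 5% when events are sparse.

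### As written, the exploratory durability model assumes equal variances and one correlation across unequally spaced visits, so its change standard errors are off if correlation falls with time

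*Protocol article*

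**What the plan says.** In the protocol article, section 3.5 (Statistical Analysis) sets out the primary model: "Fixed effects will include treatment group, time, and their interaction, with random intercepts for participants to account for within-subject variability". No random slope, residual correlation or visit-specific variance is named. Durability is then handled by extending the same family of models: "Exploratory analyses will assess the durability of treatment effects over a 1-month follow-up period, using additional time points in the mixed-effects models".

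Section 3.1 (Design and Participants) fixes the schedule. The study "will span 12 weeks plus an additional month of follow-up, with three assessments (baseline, post-intervention, and follow-up"). Taking a month as about 4 weeks, the visit pairs are about 12 weeks apart (baseline to post), 4 weeks (post to follow-up) and 16 weeks (baseline to follow-up).

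Two other statements in section 3.5 bear on how firmly the structure is set. On model choice: "Model selection will be guided by the Bayesian Information Criterion (BIC), and diagnostics will include residual checks to validate model assumptions". On software: "For linear mixed-effects models, we will use the lm4 package in R; for generalized models, the glmmTMB package will be applied" (the first package is taken here as lme4).

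Section 2.3 lists durability as the fourth exploratory aim. Section 3.6 (Expected Outcomes) defines the primary result on two visits only: "The primary outcome will be reported as the change from baseline to post-intervention in MOXO CPT total score". It also expects benefits to last to the 1-month follow-up, without naming a contrast or a rule by which this will be judged.

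**The concern.** A random intercept with independent residuals gives every visit the same variance and every pair of visits the same correlation. With two visits there is only one correlation, so no pattern is imposed. The third visit brings the restriction in, and the durability analysis is where the third visit enters.

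Under this structure all three pairwise changes receive the same pooled standard error. Measurements 4 weeks apart may well correlate more strongly than measurements 12 or 16 weeks apart. If they do, the pooled value is too small for the longest gap and too large for the shortest. The test of change from baseline to follow-up would then reject too often, and the test of change after training stops would reject too rarely. The stake is the accuracy of the intervals and p-values for the durability results, not the primary claim.

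**Working it through.** **The plan's own figure first.** Section 3.1 gives d = 0.62, z-values 1.96 and 0.84, and 20% dropout.
- n per group = 2 × (1.96 + 0.84)² / 0.62² = 15.68 / 0.3844 = 40.8, so 41.
- 41 / 0.8 = 51.25, so 52 per group and 104 in total.

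The stated 104 reproduces, and the covariance model does not enter it.

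**Inputs for the check.** From the article: a random intercept only, three visits and two-sided alpha 0.05. The correlations and standard deviations are assumptions, because the article gives none. The formulas are for large samples and complete data.

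**Formulas.** For a change between visits j and k:
- true variance per participant = σj² + σk² − 2 cov(j,k);
- variance under the random-intercept fit = 2 × (mean variance − mean covariance), the same for every pair.

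With equal variances, the ratio of model to true standard error is r = √[(1 − mean ρ) / (1 − ρjk)]. The actual type I error at a nominal 5% is 2 × [1 − Φ(1.96 r)].

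**Worked case, 0.6/0.5/0.8** (baseline–post / baseline–follow-up / post–follow-up). Mean ρ = 1.9/3 = 0.633, so 1 − mean ρ = 0.367.
- Baseline to follow-up: r = √(0.367/0.5) = 0.86; type I error 9.3%.
- Post to follow-up: r = √(0.367/0.2) = 1.35; type I error 0.8%.
- Baseline to post: r = √(0.367/0.4) = 0.96; type I error 6.1%.

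**Range, equal variances** (r, type I error):

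| Assumed correlations | Baseline to follow-up | Post to follow-up | Baseline to post |
|---|---|---|---|
| 0.6/0.6/0.6 | 1.00, 5.0% | 1.00, 5.0% | 1.00, 5.0% |
| 0.6/0.55/0.7 (mild decay) | 0.92, 7.0% | 1.13, 2.7% | 0.98, 5.5% |
| 0.6/0.5/0.8 (moderate) | 0.86, 9.3% | 1.35, 0.8% | 0.96, 6.1% |
| 0.5/0.4/0.85 (strong) | 0.83, 10.2% | 1.67, 0.1% | 0.91, 7.4% |

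A simulation of 20,000 trials per scenario with 41 completers per arm agrees. For the three decay rows it gives 7.3%, 9.4% and 10.3% for baseline to follow-up, and 2.7%, 0.8% and 0.2% for post to follow-up.

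**Unequal variances.** Take all correlations as 0.6 and standard deviations as 1, 1.2 and 1.2.
- Mean variance = (1 + 1.44 + 1.44)/3 = 1.293; mean covariance = (0.72 + 0.72 + 0.864)/3 = 0.768; model variance = 2 × 0.525 = 1.051.
- Baseline to follow-up: true variance 1 + 1.44 − 1.44 = 1.00; r = 1.03; type I error 4.5%.
- Post to follow-up: true variance 2.88 − 1.728 = 1.152; r = 0.96; type I error 6.1%.

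The errors are small and run the other way. With mild decay (0.6/0.55/0.7) and the same standard deviations, the figures are 0.94 (6.5%) and 1.07 (3.5%), so the two departures partly cancel.

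**Primary contrast.** Fitted to two visits with complete data, the model variance is 2 × [(σ1² + σ2²)/2 − cov] = σ1² + σ2² − 2 cov, which is the true value. If the primary contrast were instead read from the three-visit model, the last column of the table applies: a standard error about 2% to 9% too small under decay.

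**The case against.** The strongest reply has four parts.

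**The pattern is assumed.** No correlation or standard deviation is given for any outcome. Gentle decay does little: 0.60/0.58/0.63 gives 5.7% for baseline to follow-up and 4.2% for post to follow-up. This stands. A reader might infer that the follow-up standard errors are likely wrong in both directions, but the documents support only the conditional statement.

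**The contrasts are not named.** A reader might infer that durability rests on exactly the two change contrasts above. Sections 2.3, 3.5 and 3.6 do not say so. The between-arm difference at follow-up is just as natural. With equal variances, the random-intercept model gives its unadjusted form the correct standard error whatever the correlations. A reader might also infer that maintenance is favoured twice: once by easy rejection against baseline, and once by reading a non-significant post-to-follow-up change as persistence. The article states an expectation of maintained benefit but no such decision rule. Both objections stand.

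**The structure is not locked.** Selection by BIC and residual checks could lead to a richer model. This stands only in part. Neither provision is tied to the covariance. The named package can add a random slope but offers no residual correlation structure. Choosing the covariance after seeing the data is also weaker than fixing it beforehand.

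**An analysis plan may settle it, and the analysis is exploratory.** A condensed article can leave covariance detail to a plan that is not shown, and that plan may set it. The point here is not an omission, however. The article states a random intercept and then adds a visit to that model. The exploratory status limits the importance of the point but does not remove it.

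**Conclusion.** The point holds in a conditional form. Read plainly, the three-visit durability model assumes equal variances and one correlation across gaps of about 12, 4 and 16 weeks, and nothing in the article ties its model checks to that assumption.

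Across the assumed patterns with equal variances, the baseline-to-follow-up standard error runs from correct to 17% too small (type I error 5.0% to 10.2%). The post-to-follow-up standard error runs from correct to 67% too large (5.0% down to 0.1%). These sizes rest on correlation falling with time, equal variances, complete data and the use of change contrasts. Unequal variances can shrink or reverse them.

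The effect is confined to exploratory results unless the primary contrast is taken from the three-visit model. The sample size stands.

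**What to change.** For any model that uses all three visits, prespecify one of the following:
- a within-participant covariance left free across visits (unstructured: three variances and three covariances, in place of the random intercept), fitted in a routine that supports it, such as gls or an MMRM routine in R;
- robust standard errors that do not depend on the random-intercept structure.

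Report the between-arm difference at follow-up and the post-to-follow-up change, each with a 95% confidence interval. State also whether the primary baseline-to-post contrast comes from a two-visit or a three-visit fit.

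The cost is a few sentences of analysis text, four covariance parameters more than the two of the random-intercept model, and a different R routine from the one named. Six parameters are estimable with 104 participants and three visits. If the correlations and variances turn out equal, little is lost. If they do not, each change contrast gets its own standard error.
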